### Trial design {8}

A randomised controlled open-label multi-centre trial in a superiority framework with 1:1 allocation ratio.

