### Sample size {14}

A large registry-based study [4] on angiography-based CTO PCI revealed a procedural success rate of 87% (*n* = 3122). Two comparative studies [8, 9] on angiography-based CTO PCI versus CCTA-based CTO PCI reported success rates of respectively 90% (*n* = 30) vs. 63% (*n* = 43) and 93.5% (*n* = 187) vs. 84% (*n* = 168). Therefore, assuming a 90% success rate after 60 minutes wire manipulation in the CCTA-based CTO PCI group and 70% success rate after 60 minutes wire manipulation in the angiography-based CTO PCI group, an a priori sample size calculation revealed a minimum of 56 patients per group to detect a statistically significant difference of 20% with a power of 80% (*α* = 0.05). Assuming that <15% of patients will withdraw from the study, cross-over between groups, be lost to follow-up or have incomplete records, 65 patients will be included per group, amounting to a total of 130 patients to be included in the study.

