## Assignment of interventions: allocation

### Sequence generation {16a}

An unstratified randomisation sequence will be generated before the commencement of the study by a software algorithm (IWRS, ClinInfo SAS, Lyon, France) and to be used in assigning patients to the CT group (A) or angiography group (B) in a 1:1 ratio. The randomisation list will consist of fixed block sizes of 4, e.g. AABB–BAAB–BABA–ABBA.

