## Statistical methods

### Statistical methods for primary and secondary outcomes {20a}

Continuous variables will be reported as means, standard deviations, medians, and ranges, whereas categorical variables will be reported as numbers and proportions. Missing data will be considered separately for the calculation of proportions. Shapiro–Wilk tests will be used to assess the normality of data distributions. For normally distributed data, differences between groups will be evaluated using two-tailed *t*-tests. For non-normal distributions, differences between groups will be evaluated using Mann–Whitney *U* tests and Kruskal–Wallis tests. Effect sizes of differences between continuous variables (e.g. TIMI flow, procedure time, etc.) will be expressed using Cohen’s d, which can be interpreted as negligible (d<0.01),very small (0.01≤d<0.2), small (0.2≤d<0.50), medium (0.5≤d<0.80), large (0.8≤d<1.20), very large (1.2≤d<2.0), or huge (d≥2.0). For categorical data, differences between groups will be evaluated using chi-squared tests. All confidence intervals will be presented two-sided with a confidence level of 95%. Denominators used to calculate ratios for the intention-to-treat analysis will be the number of patients allocated to each treatment arm irrespective if they received the allocated treatment. Denominators used in the per-protocol analysis will be the number of patients that received treatment as allocated at enrolment. Denominators used in the as-treated analysis will be the number of patients that received treatment irrespective if the treatment was allocated at enrolment. Differences in success rate (successful wire crossing in ≤60 min with TIMI flow 3 is restored and residual stenosis is <30%) will be expressed in terms of absolute risk (as well as relative risk) to determine if procedures by CCTA CTO-PCA are 20% more successful compared to procedures by conventional Angiography CTO-PCI. Likewise, differences in complications between the two procedures will be expressed using absolute (as well as relative risk). A *p* value <0.05 will be deemed statistically significant. All statistical analyses will be performed using the latest version of R (R Foundation for Statistical Computing, Vienna, Austria).

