### Methods for additional analyses (e.g. subgroup analyses) {20b}

The analysis of the subgroups of this study will be based on the J-CTO score level, i.e. J-CTO = 2 versus J-CTO ≥3 [7].

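### The primary success rate gets an unadjusted chi-squared test although angiographic J-CTO class is known for every patient before allocation; stratifying on it would be a cheap gain in robustness and a modest gain in power

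*Protocol article*

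**What the plan says.** - **Test.** Protocol, Statistical methods {20a}: "For categorical data, differences between groups will be evaluated using chi-squared tests". The same section reports the difference in success as absolute and relative risk. It names no stratum or covariate for the primary comparison.
- **Randomisation.** Sequence generation {16a}: "An unstratified randomisation sequence will be generated before the commencement of the study".
- **J-CTO at baseline.** The score from conventional angiography decides eligibility (2 or more). The participant timeline {13} places it at enrolment, ahead of allocation, and {18a} requires it for all patients. It should therefore be complete and cannot be affected by the assigned arm.
- **Its meaning.** Background {6a} grades a score of 2 as difficult and 3 or more as very difficult. The same paragraph warns that scores from conventional angiography may be inadequate for predicting difficulty, duration and outcome.
- **Its use.** Additional analyses {20b}: "The analysis of the subgroups of this study will be based on the J-CTO score level", namely 2 versus 3 or more. No other analytic use is stated.

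**The concern.** The trial has 130 patients and one recorded baseline variable that the protocol itself links to procedural difficulty. Neither the allocation nor the primary test uses it. Chance can therefore give one arm a visibly harder case mix, and the primary analysis would make no allowance for it. A positive result with the easier mix in the CT arm would be open to dispute, and a harder mix in the CT arm could hide a real effect. The class boundary is already fixed for the subgroup analysis, so using it in the primary comparison needs no new data and no new definition.

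**Working it through.** **Inputs from the protocol.** Sample size {14}: "assuming a 90% success rate after 60 minutes wire manipulation in the CCTA-based CTO PCI group and 70% success rate" in the angiography group; 56 per group for 80% power at α = 0.05, raised to 65 per group. Confidence intervals are two-sided {20a}.

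**Assumptions, because the protocol gives no figures.** The share with J-CTO 3 or more is 50%. The control-arm success gap between classes is 0 to 30 points, and half that in the CT arm. Overall rates stay at 70% and 90%. A 20-point gap then means control 80% / 60% and CT 95% / 85% (J-CTO 2 / 3 or more).

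**1. The plan's own figure.** The unpooled two-sided formula gives (1.960 + 0.842)² × (0.7×0.3 + 0.9×0.1) / 0.20² = 7.849 × 0.30 / 0.04 = 58.9, so 59 per group. The pooled formula gives 62. The stated 56 is not reproduced; that is a separate matter. Exact enumeration of the chi-squared test gives power of 78.1% at 56 per group and 83.2% at 65. These are the baselines used below.

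**2. How often the arms differ.** SD of the between-arm difference in the J-CTO 3-or-more share = √(2 × 0.25 / 65) = 0.088, or 8.8 points. A difference of at least 10 points in either direction occurs in about 25% of trials, so about 13% in each direction.

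**3. What an imbalance does.** A 10-point imbalance shifts the risk difference by 0.10 × the mean of the two gaps. For a 20-point gap: 0.10 × (20 + 10)/2 = 1.5 points. For a 30-point gap: 0.10 × (30 + 15)/2 = 2.25 points. The planned effect is 20 points.

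**4. Tests compared by simulation.** For stratum s, let a_s be CT successes, n_1s and n_0s the arm sizes, N_s their sum and m_s all successes. Then CMH = [Σ(a_s − n_1s·m_s/N_s)]² / Σ[n_1s·n_0s·m_s·(N_s − m_s) / (N_s²(N_s − 1))]. The Mantel-Haenszel risk difference weights each stratum difference by n_1s·n_0s/N_s. With 300,000 simulated trials per scenario:

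| Setting | Unadjusted chi-squared | J-CTO-stratified CMH |
|---|---|---|
| 65 per arm, gap 0, all trials | 83.2% | 83.0% |
| 65 per arm, gap up to 30, all trials | about 83% | 83–86% |
| CT arm at least 10 points harder, gap 10 | 79% | 83% |
| CT arm at least 10 points harder, gap 20 | about 74% | about 84% |
| CT arm at least 10 points harder, gap 30 | 69% | 86% |

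At 56 per arm the change in power over all trials runs from about −1 to +2.6 points as the gap goes from 0 to 30 (a re-run gave +2.5 at the top).

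**5. Type I error.** With 70% in both arms, the unadjusted test rejects in about 5.2% of trials. Suppose the CT arm has drawn the easier mix by at least 10 points and the gap is 20 points in each arm. The unadjusted test then wrongly favours CT in 5.2% of those trials and CMH in 2.4%, against a nominal 2.5%.

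**6. Sensitivity.** Shares of 30%, 50% and 70%, combined with odds ratios of 1 to 5 between classes, give CMH power of 83.0–86.4% at 65 per arm and 76.7–80.9% at 56.

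**The case against.** **Nothing here is invalid.** An unadjusted chi-squared test after unstratified randomisation holds its type I error, and chance imbalance is already allowed for in its standard error. Losses when the CT arm draws the harder mix are offset by gains when it draws the easier one (about 90% power at a 20-point gap in the same simulation), which is why the average stays at 83%. All of this stands. A reader might infer that the primary test is wrong; it is not.

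**The gain rests on assumed prognostic strength.** The protocol gives no success rate by J-CTO class and no distribution of the score. It enrols only scores of 2 or more, which narrows the spread, and it doubts the predictive value of angiographic scores. This also stands, and the precision is therefore not guaranteed. A reader might reach power near 89% by assuming a 40-point control gap. With the CT gap at half that, CT success in J-CTO 2 would be 90% + 10% = 100%, which is not a credible planning case.

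**Blocks and centre.** The protocol says "The randomisation list will consist of fixed block sizes of 4", and a reader might infer that (1 + 1/3)/4, a third, of allocations can be foreseen. That requires knowing every earlier allocation on a single central list shared across centres, which the documents do not show for any operator. The number of centres does not appear in the text available, so a centre effect cannot be sized. Neither matter supports a change here.

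**An analysis plan could add adjustment.** It could, but {20a} as written already names the test and the contrast for this endpoint, so the wording there needs to change.

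**Conclusion.** The point holds as an efficiency and robustness improvement. The protocol leaves out of its primary comparison a baseline variable that it collects for everyone, describes as predictive and already splits at 2 versus 3 or more. Under the stated assumptions the average power gain at 65 per arm is between nothing and about 3 points. The stronger reason is protection in the roughly 13% of trials where the CT arm draws a clearly harder mix: about 84% power against about 74% at a 20-point gap. The size depends on how strongly J-CTO predicts success among patients scoring 2 or more, which the protocol does not quantify. If it predicts nothing, the stratified test costs about 0.2 points at 65 per arm and about 1 point at 56.

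**What to change.** Before database lock, amend {20a} so that the primary analysis of success in 60 minutes or less is a Mantel-Haenszel risk difference with 95% confidence interval and a Cochran-Mantel-Haenszel test, stratified by J-CTO 2 versus 3 or more. Keep the unadjusted chi-squared test, absolute risk and relative risk as supportive results.

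State that the stratum comes from the conventional angiogram scored before randomisation. The CT group also receives a CCTA-based J-CTO score. That score arises after allocation and in one arm only, so it must not define the strata.

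This keeps absolute risk as the effect measure; a logistic odds ratio would not. The cost is a change of wording and one further analysis step, with no new data and no change to the live randomisation list. The downside is up to about 1 point of power if J-CTO proves uninformative and only about 56 per arm are evaluable.

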### Interim analyses {21b}

Not applicable. No interim analyses are planned.

### Methods for additional analyses (e.g. subgroup analyses) {20b}

The analysis of the subgroups of this study will be based on the J-CTO score level, i.e. J-CTO = 2 versus J-CTO ≥3 [7].

### Methods in analysis to handle protocol non-adherence and any statistical methods to handle missing data {20c}

There is no analysis method for non-adherence to the protocol, as the risk for non-adherence is negligible.

### Plans to give access to the full protocol, participant-level data and statistical code {31c}

The research documents concerned by the biomedical research regulations have to be archived by all parties for a 15-year period after completion of the study, in accordance with the Good Clinical Practice guidelines. This archiving will have at least:The protocol and the potential amendments,All eCRFs,All signed informed consent forms with the list or inclusion register in correspondence,The letters of correspondence with the trial steering committee,All specific appendix,The final report of the study from the statistical analysis and the study quality control,The database used for the statistical analysis, andThe audit certificates done during the research.

## Oversight and monitoring

### Composition of the coordinating centre and trial steering committee {5d}

The research will be regulated by the standard operating procedures of ELSAN Comité Orientation Scientifique under the supervision of the main author ([name]). The trial steering committee will consist of the main author ([name]) and the Director of Scientific Research ELSAN ([name]).

### Composition of the data monitoring committee, its role and reporting structure {21a}

The data monitoring committee will be composed of at least one person from the clinical research organisation (Ecten) who will be independent from the sponsor and will have no competing interests. The role of the data monitoring committee will be to produce periodic reports to the ELSAN Comité Orientation Scientifique on the progress of the trial.

### Adverse event reporting and harms {22}

All adverse events have to be registered in the eCRF. An adverse event is considered as serious if there is death or life-threatening circumstances, inpatient or prolonged hospitalisation, persistent or significant incapacity or substantial disruption of the ability to conduct normal life functions, congenital anomaly or an event judged as serious by the Investigator.

The medical judgement of the investigator could manage to declare some other events considered as potentially serious (especially some biological anomalies). Expected serious adverse events and unexpected serious adverse events will have to be distinguished.

The investigator must, for each serious or non-serious adverse event, describe them on a form in the eCRF. The etiological diagnostic (rather than symptom), the date of the beginning, the seriousness, the intensity, the action taken with the experimental product or the study procedure, the corrective treatment administered and the causal link between treatment or procedure and serious adverse event have to be described. When the event is considered as serious, the investigator has to inform the trial steering committee immediately after having known of the events. Within 8 days after the declaration, the investigator may provide additional relevant information to the trial steering committee. If a patient declares a serious adverse event, he will be followed until the resolution of this adverse event, a stabilisation considered as tolerable or a return to the previous statement even if the patient is withdrawn from the study. Any serious adverse event associated to a study participant has to be declared from the date of consent form signature and during all the follow-up duration. If the serious adverse event is related to the study procedure, there is no time limitation of participant follow-up.

Risks related with the CT scan, object of our evaluation: as CT scan can be performed as part of standard of care for pathology diagnosis, there is no additional risk related to this investigation performed in the study. Risks will be the same risks as those related to the angiography necessary to visualise coronary arteries before and during the recanalisation procedure, as the contrast medium used is the same:IrradiationContrast-induced nephropathy in patients with renal insufficiencyAllergic reaction to radiographic contrast media

What is the frequency?Allergic reactions to iodinated contrast media are very infrequent: 1.5 events per 1000, of which 2.6% is serious [10].Incidence of renal insufficiency requiring dialysis is < 1% and the development of the complication is correlated with a dose of contrast > 100 ml, clearance of creatinine < 47 ml/min, diabetes [9].

How those risks can be managed or reduced?Reduction of cardiac rate to obtain a good quality exam with low irradiation.Anti-allergic treatment before contrast injection for the atopic patients.

Hydration for patients with chronic renal insufficiency (creatinine clearance <47ml/min), metformin-free period for diabetic patients 24h before and 48h after the contrast injection compared to the volume of contrast medium used during standard angiography and PCI, the volume of contrast medium for the CT scan is low (55ml).

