## Interventions

### Explanation for the choice of comparators {6b}

Participants will be randomised into two groups with a 1:1 allocation: the study group who will receive standard of care with the addition of preoperative CCTA-scan (CT group), and the control group that will receive standard of care (angiography group).

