### Intervention description {11a}

#### Preoperative assessment

The following assessments will be performed as part of the standard of care for the diagnosis of CTO:Conventional coronary angiographyIf symptoms and viability are not established through angiography, the patient will undergo one of the following:aStress electrocardiogram (ECG)bCardiac magnetic resonance imaging (MRI)cStress echocardiographydMyocardial scintigraphyCollection of biological markers: troponin, creatine kinase, creatinine, clearance of creatinine, haemoglobin. Preoperative angiography will be performed for all patients in ambulatory settings under local anaesthesia, with either a radial artery or femoral artery approach, with the former being the first choice if the artery is of good quality. An introducer sheath measuring 4 or 5 French (Fr.) is advanced within the artery using the Seldinger technique, and a catheter is advanced through the introducer up to the heart. A 6–8 cc iodine contrast injection in the coronary artery ostia allows visualisation of coronary artery anatomy under radiography. A picture registration is obtained and archived for planning of CTO-PCI. During the procedure heparin and nitrates are administrated.

If conventional angiography indicates a J-CTO score ≥2, the patient will be enrolled in the study, if they meet the eligibility criteria. Patients will then be randomly allocated to the CT group or angiography group. Patients in the CT group will undergo an additional CCTA scan (GE CT Revolution Scan 256; Iomeron 350 iodine contrast). The total dose length product (DLP, mGy/cm^2^) and computed tomography dose index (CTDI, mGy) will be recorded. Iodine contrast for the CCTA will be 55ml (10ml saline–55ml Iomeron 350–20ml saline at 5ml/s).

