### Provisions for post-trial care {30}

There is no anticipated harm and compensation for trial participation. Patients will undergo routine follow-ups with their cardiologist, and participation in the study will stop at 6 months after CTO-PCI.

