### Outcomes {12}

The primary objective of this study is to compare rates of successful wire crossing in ≤60 min in complex CTO (J-CTO ≥2) among the CT group and angiography group. Wire crossing will be considered successful if TIMI flow 3 is restored and residual stenosis is <30%. TIMI flow and residual stenosis will be evaluated by a pool of two cardiologists who are not directly involved in the procedure, and who are blinded to group allocation. The TIMI flow scale is classified as Grade 0 to 3 (Table 1).

**Table 1 Tab1:** TIMI flow grades

Grade 0	No flow
Grade 1	penetration without perfusion in the distal part of the artery
Grade 2	partial perfusion, the iodine contrast goes across the obstruction and fills the distal part of the artery, but the flow and the clearance of the iodine contrast are perceptibly slower if compared to the other non-occluded segments/arteries
Grade 3	complete perfusion, anterograde flow into the distal part of the artery with rapid filling and clearance if compared to the other segments/arteries.

The secondary objectives of the study are to compare:Success rates at any timeTotal time of PCI (minutes)Time of wire crossingRate of PCI complications (Major Adverse Cardiac Events, MACE): death, coronary perforation with cardiac tamponade requiring pericardiocentesis, myocardial infarction (if elevation of troponin or creatine kinase associated with change in electrocardiogram), stroke, major bleeding with loss of haemoglobin > 3 g/dl.Radiation levels during PCI expressed as transferred kinetic energy (air Kerma, Gy), dose area product (DAP, mGycm^2^), and fluoroscopy time (minutes).Volume of iodine contrast medium administered during PCI (millilitres).Cost of the PCI (euros) CTTA (CT group) Angiography Preoperative assessment, as summarised in the material invoice of every procedure.

Renal adverse events will be assessed after diagnostic coronary angiography, CCTA (CT group only), and CTO-PCI. Clinically relevant findings (like contrast allergic reaction) will be reported as adverse events. Their relationship with the CT scan or CTO-PCI will be reported. Other symptoms, such as angina CCS class, dyspnea NYHA class, MACE and renal failure will be recorded. Biologic markers, such as troponin, creatine kinase, creatinine, clearance of creatinine, and haemoglobin, will be recorded after CTO-PCI.

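### The protocol says the study CT adds no risk, although only the CT arm receives it, and the visit schedule does not secure the renal check promised after the scan

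*Protocol article*

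**What the plan says.** Adverse event reporting and harms {22} reasons that, since a CT scan may form part of standard care, "there is no additional risk related to this investigation performed in the study". It then calls the risks the same as those of angiography and lists irradiation, contrast nephropathy and allergic reaction, with frequencies.

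The design sections describe the scan differently. Explanation for the choice of comparators {6b} defines the CT arm as standard care plus the scan and the control arm as standard care alone. Under Preoperative assessment in {11a}, after allocation, "Patients in the CT group will undergo an additional CCTA scan"; "Iodine contrast for the CCTA will be 55ml", and the CT radiation dose is recorded. Eligibility criteria {10} excludes anyone already scanned before inclusion.

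On harms, Outcomes {12} states: "Renal adverse events will be assessed after diagnostic coronary angiography, CCTA (CT group only), and CTO-PCI". It adds that clinically relevant findings, such as contrast allergy, are reported as adverse events together with their relationship to the CT or the PCI.

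**The concern.** A risk statement that is wrong for the design sits in the section that governs harms. The CT is the intervention under test, and its harms can fall in one arm only, so they belong in the comparison of benefit and risk.

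The schedule raises a second problem. CT patients receive contrast twice after randomisation: at the scan and again at PCI. If renal function is not measured between the two, a creatinine rise without symptoms after the scan cannot be told apart from one after PCI. The attribution promised in Outcomes {12} would then have no data behind it for this kind of event.

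**Working it through.** No design figure is at issue, so the check compares sections and adds a little arithmetic for scale.

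**Step 1: is the scan an added exposure?** Three sections answer yes: {6b} (added to standard care in one arm), {11a} (an additional scan after allocation, with 55 ml of contrast) and {10} (no participant has already had it). A CT patient undergoes angiography, CT and PCI; a control patient undergoes angiography and PCI. The difference is one contrast injection and one CT irradiation. The statement in {22} that the kinds of risk are the same can be true while the amount of risk is higher.

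**Step 2: is the promised post-CT renal assessment scheduled?**

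| Place | What it provides | Does it separate CT from PCI? |
|---|---|---|
| Outcomes {12} | Renal events assessed after the CT; relationship to CT or PCI reported | Intended, no time point given |
| Table 2, adverse-event and renal-failure rows | Enrolment, immediate follow-up, close-out | No mark at CT or D0 |
| Table 2, blood sampling row | Enrolment, immediate follow-up | No mark at CT or D0 |
| Concomitant care {11d} | Renal function in blood taken before PCI and one day after | Only if the earlier sample follows the CT, which is not stated |
| Assessment of outcomes {18a} | Creatinine after PCI summarises renal events | No |
| Assessment of outcomes {18a} | Renal failure evaluated at the PCI visit and end of study | Possibly, but Table 2 does not mark it at D0 |

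The post-PCI sample also differs: one day after PCI in {11d}, 2 to 4 days after in Table 2.

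**Step 3: the interval on Table 2 alone.** The CT falls 1 to 30 days before D0 and the next marked check 2 to 4 days after D0.
- Shortest: 1 + 2 = 3 days.
- Longest: 30 + 4 = 34 days.

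In every case the marked check comes after the PCI contrast.

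**Step 4: scale, from the protocol's own rates.** Inputs: 65 patients per arm (Sample size {14}); allergic reactions 1.5 per 1000, of which 2.6% serious, and dialysis below 1% ({22}). One extra contrast exposure per CT patient is assumed to carry the quoted allergy rate.
- Expected allergic reactions: 65 × 0.0015 = 0.0975, about 0.1.
- Chance of at least one: 1 − (1 − 0.0015)^65 = 9.3%.
- Expected serious reactions: 0.0975 × 0.026 = 0.0025.
- Dialysis: at most 65 × 0.01 = 0.65. This is a ceiling from the stated bound, not an estimate; {22} says that "development of the complication is correlated with a dose of contrast > 100 ml", and the scan's 55 ml is below that volume.

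**The case against.** A reader might infer that CT harms will be missed or wrongly charged to PCI. The text does not support that. Outcomes {12} requires the relationship to CT or PCI to be reported. Section {22} requires every adverse event, serious or not, to be entered with its onset date, and serious events to be declared from consent, which precedes the scan. Section {18a} places a renal-failure evaluation at the PCI visit and {11d} a blood sample before PCI. The interval of up to 34 days is therefore a property of Table 2, not of the whole protocol.

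Table 2 is also a condensed journal table. None of its assessment rows is marked in the PCI column, although {18a} assesses the primary endpoint at D0. A blank cell does not prove that nothing is recorded. That stands, and it is why the finding is about reconciling sections rather than about absent safety monitoring.

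The risks are not hidden either: {22} lists them, and the disputed sentence can be read as meaning no new type of risk. Its literal wording is still wrong for this design.

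Two further inferences fail. Whether patients are misinformed cannot be judged, because the consent text is not shown. The sentence "There is no anticipated harm and compensation for trial participation" in Provisions for post-trial care {30} concerns post-trial care and compensation and does not mention the CT, so it is not a second instance of the error.

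The objection leaves one gap open: no section clearly places a renal measurement after the scan and before the PCI contrast.

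**Conclusion.** The point holds in a narrow form. The no-added-risk statement contradicts the protocol's own description of the CT as an extra exposure in one arm. The schedule does not secure the promised separation of CT from PCI effects for non-serious or laboratory-only renal changes; volunteered and serious events are already covered.

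Severity is minor. The absolute added risk is small on the protocol's own figures, and the primary endpoint is unaffected. The conclusion assumes that the Table 2 marks were read correctly and that the full protocol, not shown here, does not time the pre-PCI sample more exactly.

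**What to change.** 1. In {22}, replace the sentence with a statement that the CT arm receives one additional contrast injection and CT irradiation beyond standard care, with risks of the same type as those of angiography.
2. In Table 2, mark the adverse-event row at the CT visit and on D0 before PCI.
3. Reconcile Table 2 with {11d}, {12} and {18a}. State that in the CT arm the pre-PCI blood sample already planned is taken after the scan and serves as the post-CT renal assessment, and mark it in the table. If it is drawn on D0, it falls 1 to 30 days after the scan, so record both dates. Align the day of the post-PCI sample as well.
4. Check that the patient information agrees with the reworded risk statement. Section {30} needs no change for this point.

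The cost is one adverse-event form at visits that already exist, with no new blood sample. The trial has started, so the change needs an amendment under {25}. If it is judged to change the stated risks, that section also calls for a new information note and consent form.
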